## Abstract

**Introduction :** High horseshoe-shaped anal fistula (HHAF) is a complicated and challenging condition that presents considerable obstacles in treatment. We are presently investigating a novel surgical technique involving a combination of multi-incision and tube-dragging therapy, and laser closure (MITD-LaC) for the management of HHAF. Due to the current scarcity of rigorous evidence evaluating this approach, it is essential to perform a well-designed randomized controlled trial to compare the effectiveness of this new method with incision and thread-drawing therapy.

**Methods and analysis:** This trial is a prospective, randomized, controlled and interventional study. After preliminary screening of qualified outpatients, a total of 64 adult patients will be enrolled in the trial and randomly allocated to either the MITD-LaC group or the control group (n=32 per group). These patients will receive either MITD-LaC or incision and thread-drawing therapy. The design aims to allow for a robust comparison between the two treatment modalities. The primary endpoint is the wound healing time, while secondary endpoints include postoperative anal pain at 1, 3, and 5 days (measured with visual analogue scale), fecal incontinence score within 30 days after operation (measured with Cleveland Clinic Florida incontinence score), and the occurrence of postoperative complications within 1 month after surgery, and quality of life up to six months postoperatively (evaluated by The Quality of Life in patients with Anal Fistula Questionnaire Score).

**Discussion:** This study represents the first randomized controlled trial evaluating the short-term outcomes of MITD-LaC, thereby aiming to contribute high-quality evidence to guide clinical

practice. Moreover, this trial incorporates comprehensive outcome measures assessing both subjective and objective dimensions. Because of this multidimensional assessment, MITD-LaC offers a promising potential for broader application in the treatment of HHAF. Consequently, obtaining more definitive and authoritative evidence through scientifically rigorous clinical trials is of utmost importance in further validating this treatment approach.

# Study Protocol

## 1. Study background

Anal fistula is a prevalent, non-malignant anorectal condition characterized by the development of an abnormal channel linking the rectum or anal canal to the perianal skin, often presenting symptoms like perianal discomfort, purulent discharge, and itching. High horseshoe-shaped anal fistula (HHAF) is a type of deep posterior anal fistula that extends into the ischiorectal space and creates a horseshoe-shaped passageway on one or both sides[ 1, 2]. Due to its distinctive anatomical features, managing HHAF clinically is a formidable task, primarily because of its profound location, intricate tract structure, and involvement of the sphincter muscles[3-5].

Our current research is centered on validating the effectiveness of a surgical procedure known as Multi-Incision and Tube-Dragging Therapy combined with Laser Closure (MITD-LaC) for managing High Horseshoe-Shaped Anal Fistula (HHAF). This technique is rooted in Multi-Incision and Tube-Dragging Therapy (MITD), which involves placing multiple drainage tubes instead of traditional open incisions to maximize the preservation of the anal sphincter while ensuring adequate wound drainage. The procedure also incorporates postoperative measures, such as dragging, irrigation, and suction, to expedite the removal of necrotic tissue from the wound cavity. Compared to Incision and Thread-Drawing Therapy (ITD), MITD has demonstrated the ability to reduce postoperative complications, shorten healing time, and effectively safeguard anal sphincter function[6, 7]. Additionally, the integration of laser closure in the MITD-LaC approach contributes to enhancing its effectiveness. This technique efficiently eliminates inflammatory epithelial and necrotic tissue on the fistula wall, offering several advantages, including reduced

trauma, accelerated recovery, and reduced postoperative pain.

Up to date, MITD-LaC has not undergone a comprehensive evaluation through scientifically rigorous randomized controlled trials. Therefore, it is imperative to conduct a randomized controlled trial to compare its efficacy with that of Incision and Thread-Drawing Therapy.

## **2.Study object**

Before the enrollment, each patient will undergo magnetic resonance imaging (MRI) and transrectal ultrasound (TRUS) examinations to determine the extent of HHAF lesions and their relationship with surrounding tissues. The diagnosis of HHAF will be made and confirmed by at least two advanced radiology experts. Inclusion criteria will include male or female inpatients aged 18 to 65 years with HHAF, including complete horseshoe anal fistula and semi-horseshoe analfistula. Relevant diagnostic criteria will be referenced from the Clinical Practice Guideline for the Management of Anorectal Abscess, Fistulas in-Ano, and Rectovaginal Fistula (2016) by the American Society of Colon & Rectal Surgeons (ASCRS)[8]. Exclusion criteria will encompass patients below 18 or above 65 years of age, pregnant or lactating women, patients with malignant tumors detected through electronic colonoscopy, specific infections (such as tuberculosis, Crohn's disease, HIV infection, etc.), or severe perianal diseases like mixed hemorrhoids, anal fissure, and perianal eczema, patients with cognitive impairment or those unable to comprehend and provide informed consent, as well as patients concurrently enrolled in another clinical trial.

## **3.Study design**

This study is designed as a prospective, randomized, controlled and interventional trial. 64 patients with HHAF will be included and randomly divided into MITD-LaC group and ITD group according to different surgical treatment methods, during which clinical data related to patients will be collected and prospective analysis will be performed.

#### **4.Sample size estimation**

The sample size for this study is calculated using a two-sample comparison of means. Previous research has reported that the average healing time for patients treated with incision and thread-drawing therapy for HHAF is  $62.69 \pm 3.54$  days[9]. In our study, we assume a reduction in average healing time by 3 days in the MITD-LaC group, with an allowable error ( $\delta$ ) of 3 days and a known standard deviation of 3.54 days. The study is powered to an  $\alpha=0.05$  (type I error rate) and  $\beta=0.10$  (type II error rate), leading to  $Z_{\alpha}=1.960$  and  $Z_{\beta}=1.282$ , as determined from statistical tables. Based on the calculation, at least 25 participants are required for each group, as computed using Power Analysis and Sample Size Program 2021 (PASS, NCSS Statistical Software, Kaysville, UT, USA). To account for an anticipated dropout rate of 20%, we aim to recruit a total of 64 participants for both groups, thus allocating 32 participants per group.

Randomization will be performed using a random number table generated through SAS software, which will be based on the total number of cases. The treatment allocation will correspond to serial numbers Q01-64, creating an overall random code table. These numbers will be assigned in accordance with the order of outpatient visits.

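### The sample-size inputs printed in section 4 require 30 to 31 evaluable patients per group, not 25, so 90% power is not reached at the planned dropout

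*Protocol*

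**What the plan says.** Section 4 of the protocol (Sample size estimation) names the method: "The sample size for this study is calculated using a two-sample comparison of means". The effect is given as "we assume a reduction in average healing time by 3 days in the MITD-LaC group", and the variability as "a known standard deviation of 3.54 days". The same section sets α = 0.05 and β = 0.10 and prints the matching normal quantiles, Zα = 1.960 and Zβ = 1.282. The next sentence gives the result, attributed to PASS 2021: "Based on the calculation, at least 25 participants are required for each group".

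The section then allows for 20% dropout: "we aim to recruit a total of 64 participants for both groups, thus allocating 32 participants per group". The Abstract repeats the total: "a total of 64 adult patients will be enrolled in the trial".

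Section 4 does not say in words whether the test is one- or two-sided. The printed quantile settles it: at α = 0.05, 1.960 is the two-sided value, and a one-sided test would use 1.645. The PASS settings are not given.

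**The concern.** All the inputs and the result stand in one paragraph, and the result does not follow from the inputs. A gap of 5 to 6 patients per group is too large to be rounding.

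This is the protocol's only power statement, and it concerns the primary outcome. The figure of 25 is also the base to which the dropout allowance is applied, so the error carries through to the recruitment target of 64. If the trial ends without a significant difference, readers will judge that result against a 10% type II error. At the evaluable number the protocol plans for, that risk is about one and a half times as large.

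The mismatch also blurs the sidedness of the test. The quantile 1.960 implies a two-sided test, whereas 25 is what a one-sided 5% t-test would need. If the conflict were settled in favour of 25, the chance of a false claim of superiority in that one direction would be 5% instead of 2.5%.

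**Working it through.** **Inputs (all from Protocol section 4).** Difference δ = 3 days; standard deviation σ = 3.54 days, taken as common to both groups; Zα = 1.960; Zβ = 1.282; equal allocation; dropout 20%.

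**Step 1. The stated inputs in the two-sample formula.**

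n per group = 2 × (Zα + Zβ)² × (σ/δ)²

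= 2 × (3.242)² × (1.18)² = 2 × 10.511 × 1.3924 = 29.27, so **30 per group**.

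The exact two-sample t-test (noncentral t) has 89.7% power at 30 and 90.7% at 31, so it needs **31 per group**. The stated 25 is not reproduced.

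**Step 2. Which inputs would give 25?**

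| Setting | Normal approximation | t-test | Printed input contradicted |
|---|---|---|---|
| Two-sided 5%, 90% power (as printed) | 29.27 → 30 | 31 | none |
| One-sided 5%, 90% power | 23.85 → 24 | 25 | Zα = 1.960 |
| Two-sided 5%, 85% power | 25.003 → 26 | 27 | β = 0.10, Zβ = 1.282 |
| Two-sided 5%, 80% power | 21.86 → 22 | 23 | β = 0.10, Zβ = 1.282 |

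The one-sided t-test gives exactly 25 (power 90.5%; 89.4% at 24). Two-sided 85% power by the normal approximation gives 25.003, which becomes 25 if rounded to the nearest whole number. Each contradicts a value printed in the section.

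**Step 3. The dropout step.** 25/0.80 = 31.25, so 32 per group and 64 in total. This step is done correctly. In the other direction, 32 × 0.80 = 25.6 evaluable per group.

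**Step 4. Two-sided power for a 3-day difference.** By the normal approximation, power = Φ(δ / (σ√(2/n)) − 1.960). At n = 25: σ√(2/25) = 1.0013, 3/1.0013 = 2.996, and Φ(2.996 − 1.960) = Φ(1.036) = 0.850.

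| Evaluable per group | Normal approximation | t-test |
|---|---|---|
| 25 | 85.0% | 83.5% |
| 26 | 86.3% | 85.0% |
| 30 | 90.7% | 89.7% |
| 31 | 91.6% | 90.7% |
| 32 (no dropout) | 92.4% | 91.6% |

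With 32 recruited per group, 90% power survives the loss of 2 patients per group (6.25%) by the normal approximation, or 1 (3.1%) by the t-test.

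**Step 5. Difference detectable with 90% power at 25 per group.** 3.242 × 1.0013 = 3.25 days by the normal approximation, or 3.31 days by the t-test.

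**Step 6. Recruitment that matches the stated inputs.** 30/0.80 = 37.5, so 38 per group and 76 in total. 31/0.80 = 38.75, so 39 per group and 78 in total. The plan has 64.

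**The case against.** The strongest reply is that the trial recruits 32 per group, which is more than the 30 or 31 required. With complete follow-up, two-sided power is 91.6% to 92.4%, so the trial is not underpowered as recruited. That is correct, and the shortfall must be stated as conditional on dropout. It does not remove the problem, because the protocol itself anticipates 20% loss and sized the allowance so that about 25 per group would remain.

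A second reply is that a standard deviation described as known, together with Z values, points to the normal approximation, and that 25.6 is nearer 26 than 25. On that reading power is 86.3%, not 83.5%. The range is therefore best given as about 84% to 86%. It stays below 90% throughout.

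Thirdly, the origin of 25 is inferred. A one-sided t-test in the software is the closest match, but the settings are not reported and a slip in the power setting is also possible. Nor does anything in the protocol suggest that a one-sided analysis is intended, so the type I error consequence is only a possibility. Both caveats stand. The contradiction does not depend on its cause.

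Finally, the practical harm is moderate: power stays above 80% at the planned dropout, and neither the endpoint nor the effect estimate is affected. That is fair, but the stated power is still wrong.

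**Conclusion.** The concern holds. The figure of 25 per group does not follow from the inputs printed beside it; they give 30 (normal approximation) or 31 (t-test). At the 25 to 26 evaluable patients per group that the protocol plans for, two-sided power for a 3-day difference is 83.5% to 86.3%. That is roughly 4 to 6.5 percentage points below the stated 90%, with β of about 0.14 to 0.165. Power reaches 90% only if at most one or two patients per group are lost.

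These figures take the protocol's own difference and standard deviation as given, assume the same standard deviation in both groups, read Zα = 1.960 as a two-sided 5% test, and count each dropout as lost to a comparison of means. The correction is needed before the power statement can be relied on.

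**What to change.** Correct section 4 and keep 64 patients. Suggested text:

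> With 32 patients recruited per group and 20% dropout, about 25 per group will be evaluable. A two-sided 5% t-test then has about 84% power to detect a 3-day difference in mean healing time (standard deviation 3.54 days). Power of 90% would need 31 evaluable patients per group.

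An equivalent choice is to keep 90% power and restate the detectable difference as 3.3 days. Either way, say in words that the primary test is two-sided at 0.05, and report the software settings so that the figure can be reproduced.

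The cost is a change of wording and a less favourable power figure; no patients are added. If the sponsor wants 90% power for 3 days after 20% dropout, recruitment would have to rise to 76 to 78, which is 12 to 14 more than planned, and the totals in the Abstract and section 3 and the randomisation code range in section 4 would have to change with it.

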#### **5.Interventions**

##### **(1) MITD-LaC procedure**

A 1.5 cm incision will be made at the distal end of the perineal anal fistula, and the subcutaneous tissue will be separated to expose the fistula. Following the path of the fistula, the fistula tract will be carefully dissected to the posterior anal margin, at which point a radial incision will be made. For complete HHAF, the same procedure will be performed, extending the dissection towards the contralateral anal margin until reaching the internal opening. Subsequently, the fistula will be excised, and all surrounding inflammatory and necrotic tissue will be

meticulously removed. The fistula located above the dental line will be incised, and an optical fiber guide wire will be placed into the upper portion of the fistula tract, followed by laser vaporization and ablation of the fistula tract. After achieving hemostasis and performing thorough wound irrigation, a rubber drainage tube will be carefully inserted between the adjacent incisions and firmly secured in position. The wall of the rubber drainage tube should be perforated with multiple small holes, each approximately 2mm in diameter, thereby optimizing drainage efficiency.

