## **6. Clinical observation index**

### (1) Baseline data statistics

Baseline information (such as gender, age, height, weight, primary/recurrent, etc.) will be

recorded for both groups before surgery.

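### The single unstratified allocation list leaves fistula extent, known before enrolment, to chance balance; stratifying by it and adjusting for it would be a cheap gain in precision and credibility

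*Protocol*

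**What the plan says.** Protocol section 4 (Sample size estimation) ties the allocation to serial numbers Q01 to Q64 in one list, "creating an overall random code table". It continues: "These numbers will be assigned in accordance with the order of outpatient visits". No stratification factor, block or minimisation is named.

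Section 2 (Study object) admits two anatomical forms, "including complete horseshoe anal fistula and semi-horseshoe analfistula". It requires MRI and transrectal ultrasound before enrolment to establish the extent of the lesions. Section 5(1) gives complete fistulas a wider operation in the MITD-LaC group: "For complete HHAF, the same procedure will be performed, extending the dissection towards the contralateral anal margin until reaching the internal opening". Section 6(1) lists "primary/recurrent" status among the baseline items recorded before surgery.

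The primary outcome in section 6(2) is the time from surgery to complete epithelialization of the wound. Section 4 sizes the trial for a 3-day difference with a standard deviation of 3.54 days, and 32 patients per group after a 20% dropout allowance. The Protocol does not give the share of complete or recurrent fistulas, their effect on healing time, or the model for the primary comparison.

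**The concern.** A wider dissection plausibly leaves a wound that takes longer to epithelialize, so extent may well be prognostic for the primary outcome. It is known before allocation. A single list ignores it, and with 32 patients per group the share of complete fistulas can differ visibly between groups by chance.

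Two things are at stake. First, a visible imbalance in an obvious prognostic factor makes a small trial's result harder to believe, in whichever direction it falls. Second, if the factor is ignored in the analysis as well, its variance stays in the error term. The structure of the list has to be settled before the first patient is allocated, because an SAP cannot add stratification afterwards. It can still add adjustment.

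**Working it through.** **Inputs from the Protocol (section 4).** Difference 3 days, SD 3.54 days, Zα = 1.960, Zβ = 1.282, 25 per group before dropout, 32 per group after.

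**Assumptions, because the Protocol gives no figures.** Half the patients have complete fistulas. Mean healing time differs by D = 2, 3 or 4 days between complete and semi-horseshoe fistulas, within the total SD of 3.54. D = 0 is also possible.

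**The plan's own figure.** 2 × (3.54 × (1.960 + 1.282) / 3)² = 29.27, so 30 per group (31 by t-test), not 25. This discrepancy is a separate matter. It enters here only because two-sided t-test power is 83.5% at 25 per group and 91.6% at 32, and these are the baselines below. The dropout step is right: 25 / 0.8 = 31.25, so 32.

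**Chance imbalance.** With 64 patients, 32 of them complete, split 32/32, the number of complete fistulas in one group is hypergeometric.

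- Groups differ by 4 or more complete fistulas: probability 45.4%.
- Groups differ by 6 or more (for example 19 against 13): probability 21.1%.

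The result depends little on the assumed share. A difference of 15 percentage points or more has probability 21%, 27% and 21% when about 20%, 30% and 50% of patients are complete.

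**Effect on the observed difference.** Shift = (excess / 32) × D.

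| D (days) | Excess of 4 | Excess of 6 | Excess of 6 as share of 3 days |
|---|---|---|---|
| 0 | 0 | 0 | 0% |
| 2 | 0.25 | 0.375 | 12.5% |
| 3 | 0.375 | 0.56 | 19% |
| 4 | 0.50 | 0.75 | 25% |

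The standard error of the unadjusted difference at 32 per group is 3.54 × √(2/32) = 0.885 days, so every shift in the table is below one standard error.

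**Power if extent is adjusted for.** With half the patients complete, the residual SD is √(3.54² − 0.25 D²). The share of variance explained is R² = 0.25 D² / 3.54². Power is for a two-sided t-test at α = 0.05.

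| D (days) | R² | Residual SD | Power, 25 per group | Power, 32 per group |
|---|---|---|---|---|
| 0 | 0 | 3.54 | 83.5% | 91.6% |
| 2 | 0.08 | 3.40 | 86.4% | 93.6% |
| 3 | 0.18 | 3.21 | 90.0% | 95.8% |
| 4 | 0.32 | 2.92 | 94.5% | 98.1% |

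These figures leave out the small cost of estimating the covariate effect and of residual imbalance.

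**Separating stratification from adjustment.** A simulation (8,000 runs per cell, two binary factors each at 50%, overall list against stratified permuted blocks of 4) gave this power:

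| Per group | R² | Overall list, unadjusted | Overall list, adjusted | Stratified, unadjusted | Stratified, adjusted |
|---|---|---|---|---|---|
| 25 | 0.10 | 83.0% | 85.1% | 84.8% | 86.9% |
| 25 | 0.20 | 84.2% | 90.0% | 86.2% | 90.7% |
| 32 | 0.10 | 91.9% | 93.6% | 92.4% | 93.8% |
| 32 | 0.20 | 91.4% | 95.5% | 93.3% | 95.9% |

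At R² = 0.20, adjustment under the existing overall list gains about 6 points at 25 per group and 4 at 32. Stratification on top of adjustment adds 0.7 and 0.4. Across all the scenarios run it added between 0.3 and 1.8 points.

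Simulated type I error at R² = 0.30 and 32 per group was 5.1% for the overall list, unadjusted. For a stratified list analysed without adjustment it was 2.2%, which is conservative.

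**The case against.** Simple randomization of 64 patients is valid, and the Protocol contradicts nothing here. Chance imbalance is already allowed for in the standard error and does not inflate type I error. The prognostic effect of extent is nowhere quantified and could be zero. The wider dissection for complete fistulas is described only for MITD-LaC; section 5(2) draws no such distinction for ITD. Primary/recurrent status is recorded, but the Protocol says nothing about its effect on healing. All of this stands, and it limits the point to an optional improvement.

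A reader might go further and infer that the single list throws power away, or that the primary analysis will be an unadjusted comparison of means. The Protocol supports neither. It names the two-sample comparison of means only as the method of calculating the sample size, and it states no analysis model. Adjustment remains fully possible under the overall list and may be specified in an SAP that is not at hand. As the simulation shows, nearly all of the recoverable power comes from that adjustment and little from the structure of the list.

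What the objection does not remove is that the Protocol itself fixes the list, and the list leaves out a plausible prognostic factor that the sites will already have measured.

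**Conclusion.** The point holds as a design improvement to consider. The list is unstratified although extent is known before enrolment. If half the patients have complete fistulas, there is about a 1 in 5 chance that the groups differ by 6 or more of them. That would move the observed difference by about 0.4 to 0.75 days for a 2 to 4 day effect of extent, and by nothing if extent does not matter. Both the share and the effect are assumptions.

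The consequence is lost precision and a less credible comparison. A reader might call it bias, but under valid randomization it is not. The gain in power depends on the assumed effect of extent and is owed mainly to adjustment.

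**What to change.** Generate the SAS list in two strata, complete and semi-horseshoe, with permuted blocks of varying size. Stratify by extent only, since adding primary/recurrent status would make four strata from 64 patients and could leave small cells.

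State that the primary comparison accounts for extent and for primary/recurrent status, unless the SAP already does so. The two steps belong together, because stratifying without adjusting makes the test conservative. If allocation has already begun, leave the list alone and prespecify the adjustment before outcome data by group are examined.

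The cost is slightly more allocation logistics: two short lists in place of one, extent confirmed before a number is assigned, and group sizes that may end slightly off 32 each if a block is left incomplete. No patients, visits or measurements are added.
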